**Methods/design::**

Prospective study to optimize the health of patients with TIAs and stroke admitted to the Hamad General Hospital (PROMOTE HEALTH) is an assessor-blinded, open-label, randomized, two-arm, controlled trial. Eligible patients have IS or TIA, and an additional modifiable risk factor (Hypertension or dyslipidemia) attending the stroke ward or clinic at the Weill Cornell-affiliated Hamad General Hospital. Stroke specialists will offer the control group the currently practiced best risk factor management strategies. Whereas, in the intervention arm, with the assistance of a nurse and a pharmacist, we will make aggressive attempts to meet targets of defined risk factors. The primary outcomes are the mean difference in blood pressure (BP) and low-density lipoprotein. Whereas myocardial infarction, recurrent stroke events, and mortality serve as the study's secondary outcomes. We require 200 patients per study arm to achieve a power of 80% and an alpha level of <0.05. The Medical Research Center and the Institutional Review Board have approved the study, and it was prospectively registered in a trial registry.

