### Secondary outcomes

2.7

Recurrent events of stroke, myocardial infarction (MI), or death. Additionally, carotid plaque progression as measured on 3D Carotid Doppler imaging studies

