#### Sample size

2.8.1

Based on an estimated clinically meaningful BP difference of 10% between the two study groups. We will require 200 patients in each group (alpha error set at 0.05 and beta error at 0.20, power 80%, and an estimated dropout rate of 20%).

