#### Statistical analysis

2.8.3

We will utilize descriptive statistics to summarize the baseline data, clinical, and laboratory characteristics of our study population. Continuous variables will be summarized using means (standard deviation) and medians (interquartile range). We will utilize the ANOVA or Mann Whitney test to compare continuous data (based on data normality). Categorical variables will be compared using the Chi-squared tests. Additionally, uni and multivariate regression will be attempted in our study. All analyses will be performed using SPSS version 22.

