The earlier mentioned factors were the driving force behind the design of this trial. The primary focus of the proposed PROMOTE-HEALTH study is on improvement in risk factor management in patients presenting with a stroke or TIA. A positive study that shows that we can indeed improve risk factor management by an aggressive approach will have significant implications for health care. Especially if we can show that better risk factor management reduces the recurrence or slows the progression of the disease as measured by the parameters defined in our primary and secondary outcomes. We have carefully selected the targets for our interventions intended to be used in our study (Blood pressure and LDL cholesterol control). There is strong evidence for preventing vascular disease with appropriate management of these prevalent modifiable risk factors in this cohort of patients.^[1,2]^ Our selection of the nurses and pharmacists to deliver our intervention (aggressively controlling the modifiable risk factors was backed by evidence from other diseases. Data from 3 systematic reviews and meta-analyses (2007, 2010) demonstrated that nurse or pharmacist-led comorbidities management resulted in a better diabetes and hypertension control, respectively.^[7–9]^ Whether these benefits extend to other chronic vascular conditions is not known and is the premise of the PROMOTE-HEALTH study.

Findings from our study will carry significant weight in the future management of stroke patients locally and globally. We anticipate finishing the study by 2021. The study results will be disseminated through presentations at local, regional, and international conferences. In addition, we will publish the final results in a high-impact medical or neurology Journal.

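### The only test named that fits recurrent stroke, MI and death is chi-squared, which makes poor use of follow-up when 20% dropout is expected; a time-to-event analysis, read as exploratory, would serve better

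*Protocol article*

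**What the plan says.** Section 2.7 of the protocol article lists the secondary clinical outcomes as "Recurrent events of stroke, myocardial infarction (MI), or death", together with carotid plaque progression. Section 2.4 gives one year of follow-up, with visits monthly for three months and then every three months.

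Section 2.8.3 names ANOVA or Mann-Whitney for continuous data. For the rest it says "Categorical variables will be compared using the Chi-squared tests", followed by "Additionally, uni and multivariate regression will be attempted in our study". No model type, outcome or covariate is given for that regression.

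Section 2.8.1 bases the sample size on blood pressure alone: "Based on an estimated clinically meaningful BP difference of 10% between the two study groups". It asks for 200 per group and allows for "an estimated dropout rate of 20" per cent. Section 2.8.2 applies intention to treat to all outcomes.

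The Discussion says a positive study would have significant implications for care, and adds: "Especially if we can show that better risk factor management reduces the recurrence or slows the progression of the disease".

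**The concern.** Stroke, MI and death occur at different times within the year, and one patient in five is expected to leave before it ends. Chi-squared compares two proportions and needs a yes or no for every patient. For a patient lost at, say, five months without an event, there are two options. One is to drop the patient, which sits badly with intention to treat and discards five months of observation. The other is to record no event, which understates risk.

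If losses differ between arms, so does the understatement. That is plausible here: the trial is open label, and only the intervention arm has the dedicated nurse and pharmacist. The secondary clinical comparison could then be slightly tilted for a reason unrelated to treatment. A non-significant result might also be read as no effect on recurrence, although the trial was not sized to answer that question.

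**Working it through.** **Inputs from the article.** 200 per arm, alpha 0.05, power 80%, dropout 20% (section 2.8.1); one year of follow-up (section 2.4).

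**Assumptions.** The article gives no event rate, so I take one-year control risks of 4% to 20%. The test is taken as two-sided. Losses are taken as uniform over the year, so a lost patient contributes half a year on average.

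**The plan's own figure.** The dropout step is consistent: 160 / (1 − 0.20) = 200. The 160 itself cannot be reproduced, because no SD or base proportion is given. No event rate enters the calculation.

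**Follow-up discarded if lost patients are dropped.** Per arm, 160 × 1 + 40 × 0.5 = 180 patient-years are observed. Dropping the 40 keeps 160, so 20 / 180 = 11% of the follow-up is thrown away.

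**Bias if lost patients are counted as event-free.** Observed risk ≈ true risk × (1 − proportion lost / 2). With a true risk of 10% in both arms:

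- 20% lost in each arm: 10% × (1 − 0.10) = 9.0% in both. The risk is understated, but the risk ratio is not distorted.
- 25% v 15% lost: 10% × (1 − 0.125) = 8.75% and 10% × (1 − 0.075) = 9.25%. This is a spurious difference of 0.5 points.
- Standard error of the difference at about 9% with 200 per arm: √(2 × 0.09 × 0.91 / 200) = 2.9 points. The bias is 0.5 / 2.9 = 0.17 standard errors.

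**Power for events.** Power = Φ{[|p1 − p2|√n − 1.96 √(2p̄(1 − p̄))] / √(p1(1 − p1) + p2(1 − p2))}. For 10% v 7.5% with n = 200: (0.025 × 14.14 − 1.96 × 0.3996) / 0.3992 = −1.08, so power is 14%.

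| Assumed control risk | 25% reduction, 160 / 200 per arm | 50% reduction, 160 / 200 per arm |
|---|---|---|
| 4% | 7% / 8% | 18% / 22% |
| 10% | 12% / 14% | 40% / 48% |
| 20% | 22% / 26% | 71% / 80% |

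For 80% power at 10% v 7.5%, the same formula solved for n gives about 2,005 evaluable patients per arm.

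**Does a time-to-event test change this?** Not for power. For a 30% reduction, a log-rank test on about 180 patient-years per arm has about 11% power at 5% control risk and 18% at 10%. Chi-squared has 10% to 11% and 16% to 19% (160 to 200 per arm). The gain is in using the observed follow-up correctly.

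**The case against.** The strongest reply is that section 2.8.3 is a general paragraph in a condensed article. It does not tie chi-squared to the clinical events, and it also mentions regression. Censoring rules, competing risks and the handling of dropout for secondary outcomes commonly sit in an SAP or full protocol, which is not shown. With a fixed one-year horizon, comparing proportions is a recognised if less efficient choice. The illustrated bias is small, and it depends on counting lost patients as event-free, which no section states.

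Much of this stands. The missing detail is not itself a fault, the bias is modest, and censoring at last contact is also biased if dropout is informative. What remains is that a test has been named, and an SAP that followed the text would apply it to these events. The regression sentence is too general to supply a time-to-event analysis.

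Three stronger readings are tempting, and the documents do not support them:

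- *That chi-squared is unsafe because events are sparse.* No rate is stated. Expected events per arm fall below 5 only at pooled risks under 5 / 160 = 3.1% or 5 / 200 = 2.5%. This might happen for a single component, but nothing in the article shows it.
- *That low power for events is a design error.* These are secondary outcomes, which need not be powered.
- *That the article claims it will show reduced recurrence.* The Discussion sentence is conditional, and it offers slowed disease progression as an alternative. Rewording it is an editorial choice.

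**Conclusion.** The point holds in a limited form. The stated test is a poor match for events over a year with 20% dropout, and a better method is available at little cost. Any bias is probably small: 0.5 points, or about 0.17 standard errors, under an assumed 10% risk and losses of 25% v 15%. It is avoidable if censoring is non-informative.

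The exploratory label rests on assumed event rates, but the conclusion is not sensitive to them. Across control risks of 4% to 20%, power for a 25% reduction is between 7% and 26%. Only a halving of risk at a 20% control risk with no dropout reaches 80%. The BP and LDL primary outcomes are not affected.

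**What to change.** In section 2.8.3, replace chi-squared for these outcomes. Analyse the composite and each component as time from randomisation to first event, censored at last contact. Report Kaplan-Meier estimates and a Cox hazard ratio with 95% CI. For stroke and MI, treat death as a competing event, and use cumulative incidence in place of one minus Kaplan-Meier. State that the clinical events are exploratory because the sample size was set for BP, and that they will be interpreted through estimates and intervals.

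The cost is some extra analysis work, a check that event and last-contact dates are recorded at the visits already scheduled, and a more modest claim. Sample size, visits and treatment stay as they are. The change does not raise power, and it does not remove bias from informative dropout, so losses and their reasons should be reported by arm.

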### Quality control and trial management

2.9

The trial is approved by IRB and MRC and is following all ethical guidance (ethical Declaration of Helsinki). The study investigators will meet regularly to ensure optimal trial conduct. Additionally, a data and safety monitoring board (DSMB) will oversee the whole trial conduct with ongoing auditing and monitoring of the trial procedures. The DSMB will comprise nominated members from the Medical Research Center. All serious adverse events (SAE) will be brought to the attention of the trial team momentarily. The PI and the project manager, in turn, will update the DSMB.

Investigators will report all serious adverse events (SAE). The SAE reporting period includes the entire treatment duration and will focus mainly on medication-related side effects. Additional AEs of relevance to our study are prolonged uncontrolled hypertension, poor lipid control, and side-effects/discontinuance of medications. The DSMB will also monitor these. An interim analysis was deemed unnecessary, and thus, has not been planned in our trial (Discussed with IRB).

## Discussion

3

Stroke is the most common neurological severe diagnosis requiring hospital admission. The management and the prognosis of this entity are improving, yet it remains to be a major cause of morbidity and mortality. A report from 2017 demonstrated that stroke was the fifth leading cause of mortality in the united states.^[1]^ It is estimated that 9 out of 10 strokes are resulting from modifiable factors.^[2]^ The most common modifiable factors are hypertension, diabetes, dyslipidemia, obesity, and smoking.^[1,2]^

Prompt identification and treatment, addressing the modifiable risk factors, constitute the best stroke management strategy. However, addressing these secondary risk factors are not always successful, with recurrent strokes constituting up to a third of all new strokes.^[5]^ Another evidence suggests that there is a striking lack of awareness of the condition in the general population (less than 30% aware of the entity), and less than a third of the population is aware that hypertension and diabetes are important risk factors.^[3]^ This, in part, may explain why such strategies are ineffective. Stroke leaves the patients with considerable disability. In patients with large artery atherosclerosis, more than 50% will have moderate to severe disability 90 days after the stroke onset.^[6,4]^ Our experience over 3 decades has shown that this cohort of patients (patients with an acute IS or TIA) are a very receptive and committed to the offered medical advice.

The earlier mentioned factors were the driving force behind the design of this trial. The primary focus of the proposed PROMOTE-HEALTH study is on improvement in risk factor management in patients presenting with a stroke or TIA. A positive study that shows that we can indeed improve risk factor management by an aggressive approach will have significant implications for health care. Especially if we can show that better risk factor management reduces the recurrence or slows the progression of the disease as measured by the parameters defined in our primary and secondary outcomes. We have carefully selected the targets for our interventions intended to be used in our study (Blood pressure and LDL cholesterol control). There is strong evidence for preventing vascular disease with appropriate management of these prevalent modifiable risk factors in this cohort of patients.^[1,2]^ Our selection of the nurses and pharmacists to deliver our intervention (aggressively controlling the modifiable risk factors was backed by evidence from other diseases. Data from 3 systematic reviews and meta-analyses (2007, 2010) demonstrated that nurse or pharmacist-led comorbidities management resulted in a better diabetes and hypertension control, respectively.^[7–9]^ Whether these benefits extend to other chronic vascular conditions is not known and is the premise of the PROMOTE-HEALTH study.

Findings from our study will carry significant weight in the future management of stroke patients locally and globally. We anticipate finishing the study by 2021. The study results will be disseminated through presentations at local, regional, and international conferences. In addition, we will publish the final results in a high-impact medical or neurology Journal.
